Our previous research and other numbers of studies have shown that acute stroke patients undertaking home-based rehabilitation could achieve equal effects compared with traditional rehabilitation, in terms of effectiveness of neurologic function improvement, degree of stress relief of caregivers and safety of rehabilitation implementation.^[16–18]^ To further explore the mechanisms of home-based telerehabilitation in improving neurological functions of stroke patients, our study investigated dynamic changes of motor activated region, changes of motor functional connectivity, and structural changes of white matter fiber in patients with motor deficits by means of task-based fMRI, rs-fMRI, and DTI.

We designed this study to provide more robost evidence of the application of home-based rehabilitation on patients of stroke with motor deficits.

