#### Study design

1.1.1

The trial is an assessor blinded, paralleled randomized controlled trial (RCT). The overall flowchart is shown in Figure 1. The main aim is to explore the mechanisms of home-based telerehabilitation on improving neurological functions of stroke patients. The secondary objective is to determine the effects of home-based telerehabilitation in stroke patients.

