#### Randomization

1.3.1

In this pilot study, we aim to collect 40 patients diagnosed as stroke from the Department of Neurology, Shanghai the Fifth People's Hospital, Fudan University. Patients included in the study will be randomly allocated into 2 groups in a ratio of 1:1 after baseline assessment: home-based rehabilitation group and conventional rehabilitation group. An independent statistician will conduct randomized allocation by using a computer. The former will receive exercise training rehabilitation and electromyography-triggered neuromuscular stimulation with the assistance of caregivers at home. Specialist physicians will evaluate the recovery condition of patients via telerehabilitation system every week and give guidance on rehabilitation training and electro-stimulation therapy. The latter will receive the same rehabilitation training under the guide of specialist physicians face to face. Specialist physicians will evaluate the recovery condition of patients at outpatient clinic every week and adjust the rehabilitation strategies. Allocation concealment will be guaranteed, since allocation information will be protected in opaque sealed envelopes by a specially assigned person who is not involved in the study.

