#### Primary outcome

1.6.1

Primary outcomes will be conducted before and after rehabilitation therapies, including sum of bilateral activated volume of primary motor (M1), supplementary motor area (SMA), premotor cortex (PMC) (V_M1+SMA+PMC_); lateralization index (LI) of interhemispheric M1, SMA, and PMC (LI_M1+SMA+PMC_)(LI = (ΣV_C_ − ΣV_I_)/(ΣV_C_+ ΣV_I_), subscripts C and I refer to contralateral and ipsilateral hemisphere responses, respectively. The ΣV measures the regional activation level associated with the activated voxel); functional connectivity of bilateral M1, SMA, PMC, and the value of fractional anisotropy (FA) in corticospinal tract (CST) at ipsilesional posterior limb of internal capsule. Data will be collected before (at basement) and after (3 months) rehabilitation.

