### Data acquisition and preprocessing

1.7

Data will be acquired by a Siemens 3.0T Magnetom Trio scanner (Siemens Medical Solutions). Subjects will receive 2 MRI sessions (1 before and 1 after rehabilitation therapy). Each session included 1 rs-fMRI scan, 1 task functional scan and 1 DTI scan. For fMRI scan, parameters are TR/TE/FA = 1500 ms/30 ms/90°, 200 time points, resolution = 3.4 × 3.4 × 5 mm^3^, 21 axial slices. During rs-fMRI scan, patients will be asked to keep away with the eyes closed and think of nothing. The motor task scans used a block design paradigm consisting of alternating 30-seconds periods of performance of an isometric precision grip task and rest for 4 minutes. DTI images will be acquired with the following parameters: matrix size = 94 mm × 94 mm, field of view = 240 mm × 240 mm, 2.6 mm slice thickness, 56 slices. We acquired 1 set of 30 diffusion weighted images with a *b*-value = 1000 s/mm^2^, and 5 no diffusion weighted images.

All data will be analyzed using Functional MRI of the Brain (FMRIB's) Software Library (FSL) tools. Functional data sets will undergo slice timing correction, motion correction, scaling to percent signal change, smoothed with a Gaussian kernel of 8 mm full-width-at-half maximum, bandpass temporal filtering (0.01–0.08 Hz), and grand mean intensity normalized. A whole brain analysis of white matter integrity between groups will be performed to investigating FA. FA quantifies the degree to which water diffusion will be restricted and calculated based on the diffusion tensor. The data will be corrected for head motion and eddy current distortion, and brain extracted using Brian Extraction Tool. FA images will be then created by fitting the data to a tensor model at each voxel using DTI fit within the FMRIB's Diffusion Toolbox. Lesion will be masked out in each subject's data so that all analyses are performed on nonlesioned data.

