### Data analyses

1.9

Data analysis will be handled by independent statisticians who are blind to the groups. The statistical tests will be 2-side and at the 5% significance level. Means and standard deviation will be used for statistical description of continuous variables. For fMRI data, independent sample *t*-test or independent sample rank test will be used for grouped comparison of quantitative data. Pearson correlation coefficients (*r*) will be used to determine whether patients’ functional connectivity correlated with their FMA score and be computed after application of Fisher's *r*-to-*z* transform to yield variates that are approximately normally distributed (*z* = 0.5 ln[(1+*r*)/(1−*r*)]). All the statistical analysis will be carried out by the SPSS software (Armonk, NY). For DTI data, statistical analyses will be performed using nonparametric permutation testing (Randomize in FSL) with 5000 Monte Carlo simulations. We looked for differences in FA between the groups accounting for age, time of stroke onset, and NIHSS as regressors of no interest in the general linear model.

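### The aim and primary outcomes concern change in imaging markers, but no analysis in section 1.9 is written as an analysis of change or adjusts for the baseline value

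*Protocol article*

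**What the plan says.** **Aim.** Section 1.1.1 (Study design) states: "The main aim is to explore the mechanisms of home-based telerehabilitation on improving neurological functions of stroke patients". The Background puts this in terms of change: "our study investigated dynamic changes of motor activated region, changes of motor functional connectivity, and structural changes of white matter fiber".

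**Outcomes.** Section 1.6.1 (Primary outcome) lists activated volume, lateralization index, functional connectivity and FA in the corticospinal tract. It adds: "Data will be collected before (at basement) and after (3 months) rehabilitation". Section 1.7 confirms one MRI session before and one after therapy for each patient.

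**Analyses.** Section 1.9 (Data analyses) gives three:
- For fMRI, an independent-sample t-test, or: "independent sample rank test will be used for grouped comparison of quantitative data". The quantity compared (3-month value or change) is not named.
- A Pearson correlation of functional connectivity with FMA score, using Fisher's transform. The Abstract places the imaging-FMA correlations before and after rehabilitation.
- For FA, a permutation test of the difference between groups, with age, time of stroke onset and NIHSS as covariates.

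**Arms.** Section 1.3.1 (Randomization) says of the conventional arm: "The latter will receive the same rehabilitation training under the guide of specialist physicians face to face". Section 1.5.2 gives both groups the same electrical stimulation schedule.

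**The concern.** The aim, the outcomes and the scan schedule are longitudinal, but the named tests are not. Section 1.9 contains no change score, baseline covariate, time term or change-on-change correlation, for either fMRI or FA. Two things are at stake.

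1. **Precision.** With about 20 patients per arm, a comparison that ignores each patient's own baseline scan discards information the trial has already paid to collect.
2. **Fit to the aim.** Because the arms differ in how therapy is delivered and not in the therapy itself, the arm difference speaks to delivery mode. If the arms respond alike, which the Background leads one to expect for neurological function, the named group tests give no estimate of how the markers moved during telerehabilitation.

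**Working it through.** **Step 1: is any stated analysis written for change?**

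| Stated analysis (section 1.9) | Compares or relates | Uses each patient's baseline marker? |
|---|---|---|
| Independent t or rank test, fMRI | Groups; variable not named | Not stated |
| Connectivity-FMA correlation | Levels, before and after (Abstract) | Not as change against change |
| FA permutation model | Groups, adjusted for age, onset time, NIHSS | No baseline FA, no time term |

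None is written for change.

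**Step 2: what does the lack of baseline adjustment cost?** The article derives no sample size, so there is no planned figure to reproduce. The following is an illustration.

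Inputs from the article: 40 patients randomised 1:1 (section 1.3.1), so n = 20 per arm; two-sided 5% level (section 1.9).

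Assumptions: 80% power, equal SDs at both scans, no dropout, and a before/after correlation r between 0.3 and 0.9. The article gives no value for r.

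Unadjusted 3-month values, normal approximation: (1.960 + 0.842) × √(2/20) = 2.802 × 0.316 = 0.886 SD. With the noncentral t distribution on 38 degrees of freedom this becomes 0.91 SD.

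The other two analyses multiply the residual SD:
- change scores, by √(2(1 − r))
- baseline adjustment (ANCOVA), by √(1 − r²), on 37 degrees of freedom

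For example, at r = 0.7 ANCOVA gives 0.91 × √(1 − 0.49) = 0.91 × 0.714 = 0.65 SD. Change scores give 0.91 × √0.6 = 0.91 × 0.775 = 0.70 SD.

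Smallest detectable arm difference, in SD units:

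| r | 3-month values, unadjusted | Change scores | Baseline-adjusted |
|---|---|---|---|
| 0.3 | 0.91 | 1.08 | 0.87 |
| 0.5 | 0.91 | 0.91 | 0.79 |
| 0.7 | 0.91 | 0.70 | 0.65 |
| 0.9 | 0.91 | 0.41 | 0.40 |

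Adjustment gives the smallest figure in every row. Change scores are worse than unadjusted 3-month values at r = 0.3, equal at 0.5 and better above that. The unnamed variable therefore matters, and adjustment removes the dependence on guessing r.

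**Step 3: would within-arm change alone answer the aim?** No. Patients enter within 14 days of onset (section 1.4.1) and are rescanned at 3 months, so change within one arm mixes spontaneous recovery with therapy. It describes what happened to the markers; it does not isolate an effect of telerehabilitation.

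**The case against.** The strongest reply has four parts.

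- **An independent-sample test is not wrong in itself.** Applied to each patient's 3-month minus baseline value it is valid and uses the pairing, and the between-arm contrast is the randomised one. This stands: the text leaves the variable open and does not fix an invalid test.
- **Mechanism analyses are planned.** The connectivity-FMA correlation bears on mechanism. This stands too, although it is not written as change against change.
- **A reader might infer that the independent test will be run on before versus after scans, treating paired data as independent.** The documents do not support that. Section 1.9 speaks of a grouped comparison made by statisticians blind to the groups, and section 1.3.1 defines the two groups as the randomised arms. Power or type I error figures for such a misuse would describe something that is not planned.
- **The article condenses a fuller protocol, which may name the variable.** This limits the point but does not remove it. Section 1.9 goes beyond saying that tests will follow later: it names them by modality and lists the FA covariates, leaving out the one most directly tied to the outcome.

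**Conclusion.** The point holds as a mismatch between a longitudinal aim and analyses not written for change. It is an inexpensive improvement worth making and does not invalidate the design.

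A reader might go further and conclude that the mechanism aim goes unanswered, or that a null arm difference says nothing about mechanism. Neither follows. Imaging-FMA correlations are planned, and an arm comparison does inform whether delivery mode alters the neural response. The supportable statement is that the aim is incompletely addressed.

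On size, if unadjusted 3-month values are what is compared, baseline adjustment lowers the smallest detectable arm difference from 0.91 SD to about 0.79, 0.65 or 0.40 SD at r = 0.5, 0.7 or 0.9. If change scores are intended, the gain is smaller at high r (0.70 to 0.65 SD at 0.7; 0.41 to 0.40 SD at 0.9). All of these figures rest on the assumed correlations, equal SDs, 20 analysed patients per arm and a t-type analysis. The gain for the rank test was not computed.

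**What to change.** In section 1.9:

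1. Compare the arms on each primary imaging outcome at 3 months with adjustment for its own baseline value (ANCOVA), or use a repeated-measures model with an arm-by-time term. Name the variable analysed.
2. Add baseline FA to the FA permutation model, or run that model on 3-month minus baseline FA.
3. Report mean change within each arm with its 95% confidence interval as descriptive, stating that it includes spontaneous recovery. Separate within-arm tests should not replace the arm comparison: significance in one arm and not in the other does not show that the arms differ.
4. Correlate change in imaging markers with change in FMA score, alongside the correlations already planned.

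The cost is a few sentences, a little more analysis and one degree of freedom for each baseline covariate. No new scans or visits are needed. The one downside is that within-arm results could be over-read, which the recovery caveat is there to prevent.

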### Quality control

1.10

The researchers will receive specific training about protocols before the implementation of the study. They will try their best to make the subjects have a thorough understanding of the trial requirements, so that the subjects could cooperate better during the trial. The related rehabilitation equipment and examinations should be free to the subjects. The medication compliance of the subjects will be supervised by researchers. Superiors appointed by the sponsor will inspect and visit the process of the study at regular intervals to check the original data to ensure its accordance with the content on the case report form (CRF).

### Adverse events

1.11

Adverse events are unavoidable in the course of rehabilitation treatment. Conditions may appear in few patients during the treatment period, such as unintentional injury, rupture and bleeding of skin, muscle soreness, joint pain, and skin rash. Any adverse events (AE) during the course of rehabilitation treatment should be recorded about time of occurrence, severity, relationship of duration with intervention, and prognosis, which should be recorded in the specific CRF. Researchers should take necessary measures to deal with all AE to ensure the safety of subjects and follow-up the subjects until their physical conditions come back to normal level.

### Dissemination policy

1.12

Results of the research will be published in peer-reviewed journals and the publications will be on “open access” terms, with datasets will be accessible to the research investigators and statistical assessors. The research results will also be disseminated to the participants, stakeholders, and policymakers (Shanghai Municipal Commission of Economy and Informatization, Shanghai Municipal Commission of Health and Family Planning). The investigators will be responsible for the publication of the research to share results with broader scientific community, regardless of the magnitude or direction of effect.

## Discussion

2

We present a study design and rationale to explore the effectiveness and neural mechanism of home-based rehabilitation for stroke patients with motor deficits based on fMRI and DTI imaging. A total of 40 stroke patients will be eligibly enrolled in this clinical trial. The primary outcomes involve neural biomarkers; the secondary outcome is FMA to assess motor function; correlation between functional connectivity and motor function will also be calculated. Home-based telerehabilitation may provide an alternative means of recovery for stroke patients. Results of this trial will help to understand the neural mechanism of home-based telerehabilitation among stroke patients with hand movement disorders.
